## **Trial Protocol**

### **A Randomized Controlled Trial of Internet-delivered Emotion Regulation Individual Treatment for Adolescents with Non-suicidal Self-injury**

#### **BACKGROUND**

Non-suicidal self-injury (NSSI; also referred to as self-harm) is a common and serious global health problem and refers to direct and deliberate destruction of one's own body tissue in the absence of suicidal intent, such as cutting or burning oneself. These behaviors are prevalent in a variety of adolescent populations, ranging from approximately 14% to 45%. NSSI commonly begins between the ages of 13 and 16 years.

Repeated NSSI often results in negative emotional and interpersonal consequences for both the afflicted youths and their families. Self-harm behavior is listed in the DSM-IV as a criterion of borderline personality disorder (BPD), however many individuals who engage in repeated self-harm do not fulfill criteria for this disorder. NSSI has high comorbidity with a range of psychiatric disorders, in particular depression and anxiety disorders. Therefore, a NSSI diagnosis was included in DSM-5 in the section "conditions for further study". A Swedish study found that 6.7% of an adolescent community sample fulfilled the proposed diagnostic criteria for NSSI.

Several studies indicate that NSSI is a risk factor for suicide attempt or completed suicide. Longitudinal findings have shown that NSSI predicts suicide attempts even after controlling for a history of suicidal behavior. Although these findings are highly alarming, deaths by suicide most frequently occur during adulthood. Thus, although suicidal behavior often has its onset in adolescence, adulthood is the period with the greatest risk for death by suicide. Consequently, early effective interventions for adolescents who engage in NSSI could potentially have a suicide preventive effect. However, although NSSI is a serious condition, many individuals who engage in self-harm behaviors do not seek help. The stigma associated with NSSI is thought to be an important barrier to treatment-seeking.

#### **EVIDENCE-BASED TREATMENTS FOR NSSI**

To date no established treatments specific to self-harm exists. Randomized controlled trials (RCT) of psychological treatment effectiveness for NSSI are scarce and the results are inconclusive. It is of great concern that few therapeutic treatments have been designed and evaluated specifically for NSSI and even less research has focused on treatment for adolescents that engage in NSSI. Most studies that have been conducted in the field have included individuals that engage in self-harm behaviors both with and without suicide intent. Failing to distinguish lethal intent and the usage of vague and inconsistent terms and definitions makes it difficult to understand what exactly the different treatments have been addressing. With that said, there is some support that psychological interventions can reduce frequency of NSSI. Among the treatments that have been most frequently studied for self-harm is dialectical behavioral therapy (DBT). DBT is effective in reducing self-harm for individuals with BPD. However, DBT aims at reducing symptoms of BPD, irrespectively of self-harm, and is comprehensive and time-consuming with high costs (approximately two years of treatment including both individual therapy and skills training in group). Therefore less intensive, shorter and less expensive psychological interventions have been called for.

#### **EMOTION REGULATION GROUP THERAPY (ERGT)**

ERGT, a form of cognitive behavioral therapy (CBT), was developed to address the need for an effective short-term, focused and easily implemented treatment for adults with repeated self-harm behavior. Several researchers and treatment models (e.g. DBT) have emphasized the central role of emotion regulation in the development and maintenance of self-harm behaviors, a theory that is gaining robust scientific support. The 14-week long ERGT intervention is administrated adjunctive to treatment as usual and aims at reducing NSSI for self-harming individuals by improving emotion regulation. A newly conducted RCT on ERGT for adult women with borderline personality

disorder and self-harming behaviors showed significant effects on NSSI and other self-destructive behaviors, borderline personality disorder-symptoms, depression, anxiety, and emotion dysregulation. These findings are consistent with previous studies evaluating ERGT. The main findings from these studies were replicated in a Swedish multi-center effectiveness study conducted by this research group. Recently, an adolescent adaption of ERGT was developed by our research group; Individual Emotion Regulation Therapy for Adolescents (ERITA; EPN dnr 2014/1-31/3), which in contrast to ERGT, is given in an individual format. In this pilot study (N = 17), ratings of treatment credibility/expectancy, therapeutic alliance and the treatment completion rate were satisfactory. Intent-to-treat analyses revealed significant improvements associated with large effect sizes in past-month NSSI frequency, NSSI versatility, emotion regulation difficulties, self-destructive behaviors, and global functioning from pre- to post-treatment. Further, with the exception of NSSI versatility, all of these improvements were either maintained or further improved upon at 6-month follow-up. Finally, change in emotion regulation difficulties mediated improvements in NSSI over the course of treatment. To conclude, results suggest the acceptability, feasibility, and utility of this treatment for adolescents with NSSI-D.

#### INTERNET-DELIVERED CBT

Guided internet-delivered CBT (ICBT) has been shown to be highly effective for several mental disorders, including depression and anxiety disorders for both adults and adolescents. In ICBT, the patient follows an online treatment manual and receives support and guidance from a trained professional through online communication. While ICBT is probably as efficacious as face-to-face CBT, it allows for less therapist time per patient, it eliminates the effects of geographical distance between therapist and patient, and patients do not need to schedule appointments during their work or school day. Furthermore, ICBT can increase accessibility to psychological treatment and individuals with stigmatizing illnesses are more likely to use the internet than traditional health care to seek help, suggesting that ICBT may be suitable for NSSI. Given the advantages of ICBT, ERITA was recently adapted to be delivered over the internet; Internet delivered Emotion Regulation Therapy for Adolescents (iERITA). iERITA is currently being evaluated in an open pilot study by our research group (EPN: dnr 2015/1895-31/5). This treatment consists of two parts: one for the adolescents and one for the parents. To date, all participants (N=25) have completed treatment. Three- and 6-month follow-up assessments are still being collected. So far, 19, and 15 participants, have completed the three- and six-month follow-up measure, respectively. Also, eight of the participants in the iERITA pilot study have been included in a qualitative interview sub-study. Preliminary results of the pilot study are presented in the section "Preliminary Results".

#### AIMS AND OBJECTIVES

The overall objective of the present study is to evaluate the efficacy of adding iERITA to treatment as usual (TAU), compared to treatment as usual only. Further objectives are to investigate the possible mechanisms of change, prognostic factors, and to evaluate the cost-effectiveness of the treatment. These are the specific research questions:

- Is participation in iERITA in addition to treatment as usual, more effective than treatment as usual only, in regards to reducing NSSI, other self-destructive behaviors, emotion dysregulation, acceptance, suicidal thoughts and behaviors, depression, stress, and anxiety, for adolescents with repeated NSSI?
- Is participation in the parent program in addition to treatment as usual, more effective than treatment as usual only, in regards to enhancing the parent's perceived ability to cope with their child's negative emotions?
- Is iERITA associated with improved emotion regulation and attachment? If so, does improved emotion regulation mediate treatment outcome, and is attachment a potential competing mediator?
- Is it possible to identify predictive factors (e.g. age, NSSI frequency, BPD-symptoms, childhood trauma and psychiatric comorbidity) for treatment outcome?

- Can iERITA imply economic advantages?
- In which context (i.e. circumstances, antecedents, and consequences) does NSSI occur in, when reported in real time?

## METHOD

### DESIGN

This study adopts a randomized controlled trial (RCT) design. The study has an active control group (i.e. continuing ongoing treatment or initiating treatment as usual). The study is conducted on several Child and Adolescent Mental Health Outpatient Services (CAMHS), spread over three regions in Sweden (Stockholm, region Västra Götaland, and region Skåne). The study includes three sets of follow-up measures; post, three, and 12 months after treatment completion. The control group is measured directly after their 12 weeks of TAU, and at three-month follow-up. After they complete the three-month follow-up they are offered participation in iERITA.

### RECRUITMENT

Participants are recruited from the whole country, through advertisements in daily press, social media and information directed to primary health care specialized for child and adolescents with psychiatric problems, CAMHS, and the school health care. The inclusion and exclusion criteria are assessed through clinician administered interviews and assessments, with clinicians experienced in assessing and treating adolescents with NSSI and suicidal ideation. Once the adolescents and his/her parents, have shown interest in participating, they are allocated to the participating CAHMS closest to their home for inclusion assessment.

### INCLUSION CRITERIA

Adolescents, 13-17 years old that fulfill criteria for NSSI according to clinician-administered non-suicidal self-injury disorder index and have engaged in NSSI during the past month. One parent needs to commit to participate in the parent program.

### EXCLUSION CRITERIA

Primary psychosis, severe suicidal ideation, bipolar disorder type I, ongoing substance dependence, or comorbid axis-I-disorders (i.e. anorexia nervosa or post-traumatic stress disorder) that are considered primary and that require immediate treatment, or life circumstances that interfere with treatment (i.e. on-going abuse), or pronounced language skill deficits and learning difficulties (since the treatment format assumes normal reading and writing skills).

### MATERIAL

#### TREATMENT MANUAL

The treatment is an internet-delivered intervention (iERITA) based on the face-to-face ERITA treatment manual (EPN dnr 2014/1-31/3) and further developed after experience gained from the ongoing pilot of the internet-delivered version of the intervention (EPN: dnr 2015/1895-31/5). The treatment consists of two parts: one for the adolescents and one for the parents.

The treatment for the adolescents comprises 11 weekly modules and emphasizes the following themes: (a) the potentially paradoxical effects of emotional avoidance, (b) the emotion-regulating effect of emotional acceptance/willingness and (c) the importance of controlling behaviors when emotions are present, rather than controlling emotions themselves. Detailed individual behavior analysis is made for each individual and instructions are given on how to increase emotional awareness and gradually decrease fear of emotions and widen the behavioral repertoire. The material is accessed through a secure Internet platform where the adolescents will conduct daily registrations (of NSSI and protective factors). The adolescents will be encouraged to use a mobile app to assist them in their daily training. The mobile application also includes an individual crisis list with instructions

about who to contact in case of psychiatric deterioration (e.g. increased suicidal ideation). These features will also be available on the secure Internet platform for adolescents without access to a smart phone.

At least one parent for each adolescent will be required to participate in a parent program administrated through the Internet. The parent program will be administered in parallel to the adolescents' treatment. The parent program comprises written psychoeducation and exercises on how to support the adolescent's increased use of emotion regulation and interpersonal skills.

#### THERAPIST CONTACT

Throughout treatment, adolescents and parents have regular contact with an assigned therapist through an Internet platform, where the treatment content is also presented. The therapist provides feedback, assists in planning homework assignments, and is available for questions at any time during treatment. Text-messages to the participants will be used as reminders to work with the treatment. The therapists are licensed psychologists, psychologists under training or licensed psychotherapists with experience in treating adolescents with NSSI. All therapists undergo a mandatory four-day education where they receive information about the treatment model/manual, therapeutic stance and the Internet format. Throughout the treatment, therapists receive supervision from the research team experienced in treating adolescents with internet-delivered ERITA.

The treatment team at each CAHMS (therapists and psychiatrists) will have continuous treatment conferences with the research group during treatment, to discuss aspects of the clinical care of the participants and the treatment. The research team could consult the treatment team, but the CAHMS where the internet-therapist work is responsible for the participants' health care and security.

#### MOBILE APPLICATION

The internet platform, mobile app and the text function have been implemented using secure technology and have previously been approved by the ethics committee for several previous projects by members of this research group (dnr: 2015/1722-31; EPN dnr 2015/969-31; 2014/673-31/2; 2014/1885-31). Several security measures have been implemented with regards to the smartphone app:

- Access to the smartphone app requires a password
- A participant's account is locked to one smartphone and cannot be accessed from other smartphones
- Participant are signed out from the app after a short period of inactivity

#### MEASURES

Data, in the form of self-assessments, will be collected for all participants at baseline (weekly for four weeks) preceding the face-to-face assessment, pre-treatment, weekly during treatment, post-treatment, weekly for four weeks after treatment termination, and weekly for four weeks at three-months follow-up. Additional follow-up for participants that are randomized to iERITA will be collected 12 months after treatment is terminated (see attached flow diagram). Thenceforth, the participants will be offered the possibility to answer the same measures once every year for five years. Assessments are administered via the Internet and answers (also results of the clinical interviews) are securely stored on a database developed for this purpose and have been used in several completed and ongoing studies (dnr: 2011/1816 31/1, 2010/1993-31/4, 2011/2027-31/5, 2012/1995-31/1, 2013/1321-31/3, 2014/1-31/3, 2014/673-31/2; 2014/1885-31, 2015/1722-31, 2015/1895-31/5, and 2015/969-31). All data traffic is encrypted (2048 bit SSL) ensuring a high security level.

---

 The term "parents" refers to legal guardian(s) of the adolescent.

## Trial protocol intended for expert review

190 To measure the effect of the treatments and to screen for NSSI and psychiatric comorbidity, the  
191 following measures will be used (for a measurement chart, see figure 1):

192 1. SCREENING MEASURES  
193 FREQUENCY AND SEVERITY OF NSSI  
194 Clinician-Administered Non-Suicidal Self-Injury Disorder Index (CANDI)

195 PSYCHIATRIC COMORBIDITY  
196 Mini-Kid Internationell Neuropsykiatrisk Intervju Svensk version 6 (MINI KID), Body Dysmorphic  
197 Disorder Questionnaire (administered as an interview; BDDQ) and The Autism-Tics, AD/HD and  
198 other Comorbidities Inventory (A-TAC)

199 SUICIDAL IDEATION  
200 The suicidality module included in the MINI KID

201 SYMPTOMS OF BORDERLINE PERSONALITY DISORDER  
202 Structured Clinical Interview for DSM-IV Axis II Personality Disorders Borderline Personality Disorder  
203 Module (SCID-II-BPD)

204 GLOBAL FUNCTIONING:  
205 Childrens Global Assessment Scale (CGAS)

206 SYMPTOM SEVERITY AND IMPROVEMENT:  
207 The Clinical Global Impressions —Severity and Improvement scales (CGI-S och CGI-I)

208 2. PRIMARY OUTCOME MEASURE:  
209 SELF-HARMING BEHAVIOR  
210 The Deliberate Self-harm Inventory – youth version (DSHI-Y)

211 3. SECONDARY OUTCOME MEASURES:

212 EMOTION REGULATION  
213 Difficulties in Emotion Regulation Scale (DERS), and Difficulties in Emotion Regulation Scale – Short  
214 form (DERS-16)

215 OTHER SELF-DESTRUCTIVE BEHAVIORS AND BORDERLINE SYMPTOMS  
216 Borderline Symptom List Behavior – Behavior Supplement (BSL-Supplement), and Borderline  
217 Personality Features in Childhood (BPFS-C).

218 ANXIETY, DEPRESSION, STRESS, AND SUICIDALITY  
219 Depression, Anxiety and Stress Scale (DASS-21), and Suicidal Ideation Questionnaire (SIQ-JR).

220 LIFE QUALITY  
221 Kidscreen-10^50

222 DEGREE OF ACCEPTANCE TOWARDS EMOTIONS  
223 Acceptance and Action Questionnaire (AAQ-II)

224 DEGREE OF ANXIOUS AND AVOIDANT ATTACHMENT TOWARDS PARENT  
225 Short form of the Experience in Close Relationships Scale – Revised Child version

226 4. BASELINE MEASURE

227 SLEEP  
228 Insomnia Severity Index (ISI)

229  
230 5. TREATMENT PROCESS VARIABLES:

Working Alliance Inventory–short form (WAI), the Credibility/Expectancy Questionnaire (CEQ), the Client Satisfaction Questionnaire (CSQ), the Adverse Event Protocol (AEP), and the clinician rated ICBT adherence scale (PIAS)

## 6. PARENT MEASURES:

### PARENT VARIABLES

History of NSSI and Suicidal Ideation (SITBI-SF-SH) and the Coping with Children's Negative Emotions Scale Adolescent Version (CCNES-A).

## 7. HEALTH ECONOMICS

Trimbos and Institute of Technology Cost Questionnaire for Psychiatry (TIC-P)

## POWER

The sample size of this study was determined based on the observed treatment effects in the uncontrolled pilot study of iERITA (EPN: dnr 2015/1895-31/5). Based on an expected average difference of two self-harming episodes between the groups at post-treatment yields a total sample size of 140 participants with a power of 82% given alpha .05, after the 12-week follow-up. Given an estimated attrition rate of 15%, we aim to include 165 adolescents.

The power refers to a 0.05-level Wald test for the interaction between a binary treatment and linear time in a zero-inflated negative binomial regression model at a 0.05 level. The power was estimated with 200 bootstrap samples. The data for the treated group were obtained by sampling with replacement from the available pilot data. The data for the control group was obtained by adding the difference to the count of a bootstrap sample from the iERITA pilot data on the 25 treated patients.

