#### PRIMARY ANALYSIS

The primary outcome analysis will include treatment group (ERITA , TAU) and weekly reports of NSSI frequency measured once every week 4 weeks prior to treatment start, once every week during treatment, and once every week four weeks after treatment termination. Regression analysis modelled for count data will be used to estimate trend over time. Four weeks after treatment termination will be considered primary endpoint. Pairwise contrasts (group x time interaction) from the regression model will be used to evaluate between-group differences at primary endpoint (4 weeks after treatment termination).

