## Power and Sample Size

### A Randomized Controlled Trial of Internet-delivered Emotion Regulation Individual Treatment for Adolescents with Non-suicidal Self-injury

[name]

September 15, 2017

Figure 1. Histogram of episodes8 (yellow bars) and predicted probabilities from a zero-inflated negative binomial model (red dots)

[figure not shown]

698     Figure 2. Box plots of the distribution of episodes8 over time in weeks

[figure not shown]

699

700

701 Figure 3. Estimated trend of the rate of episodes8 over time with a zero-inflated negative binomial model.

[figure not shown]

702

703

704

Table 1. Estimated power to detect a different slope between the treated and control groups corresponding to different sample sizes and differences in the expected count between groups after the 12-week follow-up. The power refers to a 0.05-level Wald test for the interaction between a binary treatment and linear time in a zero-inflated negative binomial regression model at a 0.05 level. The power was estimated with 200 bootstrap samples. The data for the treated group were obtained by sampling with replacement from available pilot data from an earlier study on 25 treated patients. The data for the control group was obtained by adding the difference specified in the table to the count of a bootstrap sample from the pilot data on the 25 treated patients.

| Difference
between groups
in average count
after 12 weeks | Sample size
per group | Estimated
power |
|--------------------------------------------------------------------|--------------------------|--------------------|
| 1                                                                  | 150                      | 0.80               |
| 2                                                                  | 70                       | 0.82               |

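### The only power figure (82%) is for a slope interaction with the effect set at 12 weeks; it does not cover the primary test as written, a contrast four weeks after treatment

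*Protocol*

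**What the plan says.** **Power section.** The sample size rests on an "expected average difference of two self-harming episodes between the groups at post-treatment", which yields "a total sample size of 140 participants with a power of 82% given alpha .05, after the 12-week follow-up". The test is a 0.05-level "Wald test for the interaction between a binary treatment and linear time in a zero-inflated negative binomial regression model". Power was estimated from 200 bootstrap samples of pilot data on 25 treated patients, with the control arm formed by adding the difference to resampled counts.

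**Power and Sample Size appendix, Table 1.** The caption describes "Estimated power to detect a different slope between the treated and control groups" for various sample sizes and "differences in the expected count between groups after the 12-week follow-up". The row used is a difference of 2, 70 per group, power 0.82.

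**Statistical Analyses, opening paragraph.** The primary end-point for all outcomes is post-treatment.

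**Primary Analysis.** The model uses weekly NSSI reports for four weeks before treatment, throughout treatment and for four weeks afterwards. It is a count regression estimating a trend over time. The primary endpoint is four weeks after treatment termination, and "Pairwise contrasts (group x time interaction) from the regression model will be used to evaluate between-group differences at primary endpoint". Treatment lasts twelve weeks (Procedure), so this is about week 16.

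**The concern.** A power figure should belong to the test that decides the trial, at the time point where it is decided. Here the powered quantity is tied to a difference at 12 weeks, while the primary analysis is evaluated four weeks later. Nothing states what difference is expected at that point, or whether the 12-week difference is assumed to persist. The primary contrast is also not pinned down enough to tell whether it is the powered test in another form.

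At stake is how the result is read. The 82% is the sole statistical justification for the sample size. If the contrast in Primary Analysis is the deciding test, a non-significant result would be judged against a power that was never worked out for it.

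**Working it through.** **1. What reproduces.** Enrolment: 140 / (1 − 0.15) = 164.7, rounded up to 165, as stated. The Power section and Table 1 agree (70 per group, 0.82). The 0.82 itself cannot be recomputed, because the pilot data are not given. Its simulation standard error is √(0.82 × 0.18 / 200) = 0.027, a 95% interval of about 0.77 to 0.87.

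**2. The time points side by side.**

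| Place in the protocol | Time point |
|---|---|
| Power | post-treatment / after 12 weeks |
| Table 1 | after 12 weeks |
| Statistical Analyses, opening | post-treatment |
| Primary Analysis | four weeks after treatment ends |

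Three agree and one does not. The odd one out is the section that defines the deciding test.

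**3. Is the contrast a different test from the slope?** That depends on details the protocol does not fix. In a simulated log-linear count model with linear time (Poisson GEE, 70 per group), the slope interaction gave z = −7.99. The baseline-to-week-12 and baseline-to-week-16 change contrasts gave the same z = −7.99, since each is the slope coefficient times a constant. The between-group difference in level at week 16 gave z = −4.67. With linear time a change contrast is therefore the slope test, and a level contrast is not.

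**4. How far could the power move?** This is an illustrative linear-Gaussian approximation, not the plan's zero-inflated model. Assumptions:
- Two-sided alpha of 0.05 (the protocol does not state sidedness).
- Weekly residual variance 1, and true individual 12-week change with variance g, from 0 to 2.
- The two-episode difference is reached at week 12 and held to week 16.

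Calibration: power 0.82 means a non-centrality of 1.960 + 0.915 = 2.875 for the slope over weeks 0 to 12. The variance of that slope's 12-week change is 144/182 + g = 0.791 + g. For another contrast with residual variance D,

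power = Φ(2.875 × √[(0.791 + g)/(D + g)] − 1.960).

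| Contrast | D | g = 0 | 0.5 | 1 | 2 |
|---|---|---|---|---|---|
| Week 16 vs one baseline week | 1 + 1 = 2 | 0.44 | 0.54 | 0.60 | 0.67 |
| Week 16 vs mean of four baseline weeks | 1 + 1/4 = 1.25 | 0.63 | 0.69 | 0.73 | 0.76 |
| Mean of weeks 13–16 vs mean of four baseline weeks | 1/4 + 1/4 = 0.5 | 0.95 | 0.90 | 0.88 | 0.86 |
| Slope over weeks −4 to −1 and 1 to 16 | 0.346 | 0.99 | 0.94 | 0.91 | 0.88 |

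Example, first row, g = 0: √(0.791/2) = 0.629; 2.875 × 0.629 − 1.960 = −0.15; Φ = 0.44.

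For the last row, the sum of squares of time is 732.2. A straight line fitted to a ramp that stays flat before week 0 and after week 12 recovers 0.754 of the effect per 12 weeks, so D = (144/732.2)/0.754² = 0.346. That row also assumes individual change follows the same ramp. If individual trends instead run straight through the window, g = 2 gives Φ(2.875 × 0.754 × √[2.791/(0.197 + 2)] − 1.960) = 0.69.

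**5. If the effect faded.** With 1.5 episodes at week 16 instead of 2, the second row is multiplied inside by 0.75 and gives 0.40 to 0.52. This is a sensitivity check, not a prediction.

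**The case against.** The strongest reply is that there is no mismatch of test at all. Primary Analysis calls its contrast a group-by-time interaction from a model that estimates trend. If time enters linearly, a baseline-to-endpoint contrast is the same Wald test as the powered slope, as step 3 shows. This stands: a reader might infer that the trial was powered for one kind of test and will be decided by another, and the text does not establish that. It does not close the matter, because Primary Analysis never says time is linear and speaks of between-group differences at a named point. Even an identical form of test, run over a longer window, has a power that depends on what happens after week 12.

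Second, the power section agrees with the opening of Statistical Analyses, so the 82% does match one of the protocol's two endpoint statements. That is correct, and it makes this partly a conflict between two paragraphs of the analysis section.

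Third, time coding and the exact contrast are commonly left to a statistical analysis plan, which is not at hand. That is fair, and their absence is not the point here. The primary time point, however, is fixed in the protocol in two different ways.

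Fourth, the protocol does not say which weeks entered the simulation, so it cannot be asserted that pre- or post-treatment weeks were left out. The only evidence on persistence also points away from fading: the pilot effect on NSSI was d = 0.88 at post-treatment and d = 1.28 at six months. It is uncontrolled, with 15 participants at six months so far, but nothing in the document supports a fading effect.

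**Conclusion.** The point holds in a limited form. The protocol's single power figure is for a treatment-by-linear-time interaction with two episodes' difference at 12 weeks. Primary Analysis sets the decision at four weeks after treatment and gives no assumed difference there. The 82% therefore cannot stand as the power of that test as written.

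A reader might infer that the trial is underpowered. The documents do not support this. With the effect held, single-week-16 contrasts give 0.44 to 0.76, but pooling the four post-treatment weeks gives 0.86 to 0.95. A slope over the full window gives 0.88 to 0.99 under one assumption about individual trends, and as little as 0.69 under another. The true figure could be below or above 82%.

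All these values rest on a Gaussian approximation, an assumed range for individual variation and calibration to the stated 0.82. They show how much depends on the unstated choice, not what the power is. No arithmetic in the protocol is wrong and the sample size is not shown to be inadequate, so this is a correction that should be made rather than a flaw that undermines the design.

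**What to change.** 1. Settle one primary time point, and make Power, the opening of Statistical Analyses, Primary Analysis and Table 1 all state it.
2. Then do one of two things:
   - name the treatment-by-linear-time interaction as the primary test in Primary Analysis, with the weeks it uses; or
   - keep the contrast, and rerun the simulation for it with the same data window, model and time point, within-patient correlation, and a stated assumed difference at that time point. Replace the 82% in the Power section and in Table 1 with the result.

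If the contrast is kept, say whether four weeks after treatment means the single report at about week 16 or the four post-treatment reports together. In the table above that choice moves the figure most.

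The cost is a few hours of simulation and some rewording. The new figure may be less favourable. Recruitment can stay at 165.
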